### Statistics and sample size calculation

#### Sample size

Sample size calculation was performed by using a two-sided two-sample t-test for non-inferiority. Treatment strategies will be considered non-inferior if the difference between groups remains within the minimum clinical significance (5 points) for the bowel function subdomain based on EPIC. With an alpha = 0.05 and a standard deviation = 5, 23 patients in each arm are needed for a power = 0.90. Since the London Regional Cancer Program covers a large catchment area, 20% are estimated to be lost to follow-up, therefore 29 patients in each arm (29 × 0.8 = 23.2) or 58 total patients will be required.

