### Endpoints

#### Primary endpoint

Late bowel toxicity and quality of life measured using the Expanded Prostate Cancer Index Composite (EPIC) bowel function subdomain at 1 year post-treatment

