### Subject discontinuation and withdrawal

Subjects may voluntarily discontinue participation in the study at any time. If a subject is removed from the study, the clinical and laboratory evaluations that would have been performed at the end of the study should be obtained. If a subject is removed because of an adverse event, they should remain under medical observation as long as deemed appropriate by the treating physician.

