#### Analysis plan

Patients will be analyzed in the groups to which they are assigned (intention-to-treat).

Comparisons between treatment arms for acute and late urinary, bowel and sexual quality of life end points will be performed using the two-sample t-test for non-inferiority. Quality of life data is anticipated to be normally distributed. In the event such data is not normally distributed, the Wilcoxon rank sum test for non-inferiority will be substituted as appropriate. Similarly, IPSS data is anticipated to be normally distributed and will follow similar methodology. Differences in urinary, bowel and sexual toxicity and PSA response rate at 4 years post-treatment between treatment arms will be compared using the Chi–square test or Fisher’s exact test as appropriate. Time-to-event end points (e.g. overall survival) will be compared between treatment arms using Kaplan-Meier estimates and the log-rank test.

In the event the non-inferiority criteria is met for the primary end point (late bowel function quality of life based on EPIC), a secondary analysis to investigate superiority of the experimental arm will take place. This will be performed using the two-sample t-test (or Wilcoxon rank sum test as appropriate as similarly discussed above). A 5-point difference in scores will be considered a clinically meaningful change.

For each quality of life domain and IPSS data, linear mixed effects models will be generated to test for differences between treatment arms over time. Cox proportional hazards univariable and multivariable regression models will be used to identify baseline factors predictive of time-to-event end points (e.g. overall survival).

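### The non-inferiority decision rests on a two-sample t-test of the 1-year EPIC score with 20% expected loss, although the already planned mixed model would use the forms of men who lack that score

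*Protocol article*

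**What the plan says.** The Protocol article fixes the following.

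- **Endpoint** (Primary endpoint): "Expanded Prostate Cancer Index Composite (EPIC) bowel function subdomain at 1 year post-treatment".
- **Sizing** (Sample size): "Sample size calculation was performed by using a two-sided two-sample t-test for non-inferiority". The criterion is that "the difference between groups remains within the minimum clinical significance (5 points" on the bowel function subdomain. "With an alpha = 0.05 and a standard deviation = 5, 23 patients in each arm are needed for a power = 0.90".
- **Loss** (Sample size): "20% are estimated to be lost to follow-up", which the same sentence attributes to the centre's large catchment area. This takes 23 per arm to 29, or 58 in total.
- **Primary test** (Analysis plan): a two-sample t-test for non-inferiority, with a Wilcoxon rank sum test if the data are not normal. No baseline covariate is mentioned.
- **Population** (Analysis plan): "Patients will be analyzed in the groups to which they are assigned (intention-to-treat").
- **Longitudinal model** (Analysis plan): for each quality of life domain, "linear mixed effects models will be generated to test for differences between treatment arms over time". The non-inferiority decision is not assigned to it.
- **EPIC schedule** (Table 2): baseline, first and last day of WPRT, 6 weeks, 6 months and 12 months, then on to 60 months.
- **Removal** (Subject discontinuation and withdrawal): if a subject is removed, "the clinical and laboratory evaluations that would have been performed at the end of the study should be obtained". Men removed for an adverse event stay under medical observation. Questionnaires are not named.

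**The concern.** A two-sample t-test on a score at one visit uses only men who have that score, unless values are imputed. The sizing counts patients in the same way: the expected losses are replaced by recruiting more men, and the power rests on the 23 who remain. A man who completes EPIC at baseline, during treatment, at 6 weeks and at 6 months, and then misses month 12, adds nothing to the decision.

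That is inefficient. It is also valid in general only if missing the 1-year form is unrelated to bowel function, including bowel function already recorded on earlier forms. The trial has features that make this assumption worth protecting. The outcome is patient-reported in an open-label trial. The Background says that long-term bowel toxicity with this approach is unknown, and that one earlier single-arm study of hypofractionated WPRT stopped early after more late toxicity than anticipated. The discontinuation section foresees removal for adverse events and does not say that EPIC continues afterwards.

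At stake is the error that a non-inferiority trial most needs to control: declaring the experimental schedule acceptable on bowel function when it is worse by the full margin.

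**Working it through.** **Inputs from the Protocol article:** margin 5 points, SD 5, alpha 0.05 two-sided (0.025 one-sided), power 0.90, 23 evaluable per arm, 20% loss, 29 per arm randomized.

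**Assumptions, not in the document:** a true difference of 0 for the power calculation, and the gap *d*, defined as how many points lower the lost men in Arm 2 would have scored than the retained men. The document gives no value for *d*, so a range is shown.

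**1. Reproducing the plan's figures.**
- SE = SD × √(2/n) = 5 × √(2/23) = 1.474.
- With 44 degrees of freedom and one-sided alpha 0.025, the noncentral t power at n = 23 is 0.912. At n = 22 it is just under 0.90. So 23 per arm reproduces. (One-sided 0.05 would give 18.)
- 23 / 0.8 = 28.75, rounded up to 29 per arm, 58 in total. This reproduces too.
- Expected without a 1-year score: 29 × 0.2 = 5.8 per arm, 11.6 overall.

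**2. Bias of a test on observed 1-year scores.** The full Arm 2 mean is 0.8 × m + 0.2 × (m − d) = m − 0.2d, where m is the mean of the retained men. The observed mean is therefore too high by 0.2d. The same holds in Arm 1 with its own gap, so

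net bias toward non-inferiority = 0.2 × (gap in Arm 2 − gap in Arm 1).

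**3. False non-inferiority at a true difference of −5**, with loss in Arm 1 unrelated to outcome. This is the probability that a noncentral t with 44 degrees of freedom and noncentrality bias/1.474 exceeds the critical value 2.015.

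| Assumed Arm 2-only gap (points) | Bias (points) | Noncentrality | False non-inferiority |
|---|---|---|---|
| 0 | 0 | 0 | 2.5% |
| 2.5 | 0.5 | 0.339 | 5.2% |
| 5 | 1.0 | 0.678 | 9.7% |
| 10 | 2.0 | 1.356 | 26% |

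**4. Dependence on direction.** Gaps of 5 and 5 give 0.2 × (5 − 5) = 0. Gaps of 5 in Arm 2 and 10 in Arm 1 give 0.2 × (5 − 10) = −1.0 point, which works against non-inferiority.

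**5. How much selective loss would overturn a typical success.** With an observed difference of 0, the 95% half-width is 2.015 × 1.474 = 2.97 points, which leaves 5 − 2.97 = 2.03 points to the margin. With 20% lost and selection in Arm 2 only, the lost men would have to score 2.03 / 0.2 = about 10 points below the retained men to use that up.

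**The case against.** The strongest reply is that only a journal article is at hand. Imputation rules and sensitivity analyses for missing scores usually sit in the analysis plan, and their absence here is no fault. That stands. For the same reason, a reader might infer that the plan restricts the primary test to men with a 1-year form. No section says so. It follows from the choice of test and the sizing only if nothing is imputed.

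Three further inferences are tempting, and the document does not support them.

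- *That the intention-to-treat claim is false.* The sentence defines the term as analysis by assigned group. Missing scores do not breach it, and the 20% loss is openly declared.
- *That loss will push the result toward non-inferiority.* The reason given for loss is distance. The bias needs loss related to bowel outcome and more selective, or heavier, in Arm 2. Gaps of 5 and 10 points are one and two planning SDs, and nothing in the article supports a particular value.
- *That removal for an adverse event loses the 1-year EPIC.* The section asks for end-of-study evaluations and continued observation. It neither names nor excludes questionnaires. Its collection is unsecured rather than lost.

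It can also be said that men unwilling to complete questionnaires are excluded, that the mixed model is already planned, and that choosing between two planned analyses is a matter of preference. The first two are true. The third is not persuasive. The article itself ties the decision to the test that sets aside the earlier forms and baseline, while planning a method that can use them. That is a choice stated in the document, not a detail left for later.

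**Conclusion.** The point holds as a weakness in the stated choice of primary analysis, and a change should be made. It is not a contradiction or a demonstrated bias. What is firm is that the decision is tied to a t-test at one visit without baseline adjustment, that about 6 of 29 men per arm are expected to lack that score, and that unless values are imputed their other EPIC forms do not enter the decision.

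The size of any bias is conditional. False non-inferiority stays at 2.5% if loss is unrelated to outcome. It reaches 5.2%, 9.7% or 26% only under the assumed Arm 2-only gaps of 2.5, 5 or 10 points, with 20% loss, SD 5, 23 per arm and a true difference exactly at the margin. Equal gaps with equal loss cancel, and a larger gap in Arm 1 makes the test conservative.

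**What to change.** 1. In the Analysis plan, make the month-12 Arm 2 minus Arm 1 contrast from the planned linear mixed model the primary analysis. Include the post-baseline EPIC visits to month 12, baseline EPIC bowel function as a covariate, and all randomized patients with any post-baseline form. Declare non-inferiority if the lower limit of the 95% interval lies above −5. Keep the two-sample t-test as a sensitivity analysis.
2. In Subject discontinuation and withdrawal, state that EPIC collection continues through month 12 for patients who stop protocol treatment but do not withdraw consent to follow-up.

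The cost is a change of wording and modest extra modelling. No patients, visits or forms are added, and 58 does not change. The mixed model assumes that data are missing at random given the recorded scores. It therefore reduces, but does not remove, bias from loss that depends on bowel function never recorded. How to probe that assumption can be left to the analysis plan.

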#### Analysis plan

Patients will be analyzed in the groups to which they are assigned (intention-to-treat).

Comparisons between treatment arms for acute and late urinary, bowel and sexual quality of life end points will be performed using the two-sample t-test for non-inferiority. Quality of life data is anticipated to be normally distributed. In the event such data is not normally distributed, the Wilcoxon rank sum test for non-inferiority will be substituted as appropriate. Similarly, IPSS data is anticipated to be normally distributed and will follow similar methodology. Differences in urinary, bowel and sexual toxicity and PSA response rate at 4 years post-treatment between treatment arms will be compared using the Chi–square test or Fisher’s exact test as appropriate. Time-to-event end points (e.g. overall survival) will be compared between treatment arms using Kaplan-Meier estimates and the log-rank test.

In the event the non-inferiority criteria is met for the primary end point (late bowel function quality of life based on EPIC), a secondary analysis to investigate superiority of the experimental arm will take place. This will be performed using the two-sample t-test (or Wilcoxon rank sum test as appropriate as similarly discussed above). A 5-point difference in scores will be considered a clinically meaningful change.

For each quality of life domain and IPSS data, linear mixed effects models will be generated to test for differences between treatment arms over time. Cox proportional hazards univariable and multivariable regression models will be used to identify baseline factors predictive of time-to-event end points (e.g. overall survival).

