**Fig. 1 Fig1:**
[figure not shown]
Study schema. Abbreviations: NCCN – National Comprehensive Cancer Network; MSKCC – Memorial Sloan Kettering Cancer Center

The study will employ a 1:1 randomization between Arm 1 and Arm 2 in a permuted block design without stratification with the size of the blocks known only to the statistician.

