### Follow-up evaluation and assessment of efficacy

The follow-up schedule is shown in Table 2. Day 1 of follow-up will correspond with the last day of WPRT. Additional imaging or laboratory investigations should be carried out at the discretion of the oncologist, based on findings in the history or physical examination. Additional treatment (e.g. salvage treatment with surgery or further radiotherapy) is at the discretion of the treating physicians, and will be captured in the case report form.

**Table 2 Tab2:** Study follow-up schedule

	Baseline^a^	First day of WPRT	Last day of WPRT	6 weeks post-WPRT	Follow up (months)^b^						
					6	12	18	24	36	48	60
Physical Examination	X			X	X	X	X	X	X	X	X
Imaging	X										
PSA	X				X	X	X	X	X	X	X
EPIC	X	X	X	X	X	X	X	X	X	X	X
IPSS	X	X	X	X	X	X	X	X	X	X	X
CTCAE	X	X	X	X	X	X	X	X	X	X	X
Survival and disease status					X	X	X	X	X	X	X
EQ-5D and PORPUS-U	x			x		x		x			

*Abbreviations*: *WPRT* whole pelvis radiotherapy, *PSA* prostate specific antigen, *EPIC* Expanded Prostate Cancer Index Composite, *IPSS* International Prostate Symptom Score, *CTCAE* Common Terminology Criteria for Adverse Events, *EQ-5D-5L* EuroQOL 5-Dimension 5-Level, *PORPUS-U* Patient-Oriented Prostate Utility Scale

^a^Baseline assessments to be completed prior to high-dose-rate brachytherapy

^b^Follow-up schedule determined based on day of last WPRT treatment

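### The primary non-inferiority test leaves out the baseline EPIC bowel score that the trial collects anyway: the t-test is valid, but precision and protection against chance imbalance are given away

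*Protocol article*

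**What the plan says.** All references are to the protocol article.

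- **Primary endpoint.** Late bowel toxicity and quality of life "measured using the Expanded Prostate Cancer Index Composite (EPIC) bowel function subdomain at 1 year post-treatment". No change from baseline is defined.
- **Analysis plan.** Arm comparisons for the acute and late quality of life "end points will be performed using the two-sample t-test for non-inferiority". If the data are not normal, "the Wilcoxon rank sum test for non-inferiority will be substituted as appropriate". If non-inferiority is met, superiority is tested with the two-sample t-test or Wilcoxon test. No covariate is named in any of these steps. Linear mixed effects models are also planned for each quality of life domain, to look at arm differences over time.
- **Sample size.** "Sample size calculation was performed by using a two-sided two-sample t-test for non-inferiority". The margin is 5 points, the SD 5, alpha 0.05 and power 0.90. This gives 23 per arm, raised to 29 per arm for 20% loss to follow-up.
- **Baseline.** Pre-treatment evaluation has EPIC completed on the day of enrollment. The footnote to Table 2 reads "Baseline assessments to be completed prior to high-dose-rate brachytherapy". Patients who cannot or will not complete the questionnaires are excluded.
- **Allocation.** A "permuted block design without stratification".

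**The concern.** A patient's bowel function before treatment is likely to predict bowel function a year later. An unadjusted comparison leaves that predictable part of the variation in the error term, so the confidence interval that must stay inside the 5-point margin is wider than it need be.

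With about 23 evaluable patients per arm and no stratification, the arms can also differ by chance at baseline, and part of that difference reappears at 1 year. A gap against the hypofractionated arm makes non-inferiority harder to show; a gap in its favour makes it easier. The data needed to remove this are already being collected.

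**Working it through.** **Inputs from the article (Sample size):** margin 5, SD 5, two-sided alpha 0.05 (taken as one-sided 0.025 for non-inferiority), 23 evaluable per arm, 29 randomized per arm.

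**Assumptions not in the article:** correlation ρ between baseline and 1-year score of 0.3 to 0.7; baseline SD of 5; a true SD of 7.5 as an adverse scenario. All figures below use 23 per arm.

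**1. The plan's own figure.** Exact noncentral-t power, true difference 0, noncentrality 5 / (5·√(2/n)):
- n = 22: 0.8997
- n = 23: 0.9125

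So 23 is the smallest n that reaches 0.90, and 23 / 0.8 = 28.75 rounds up to 29. The stated 23 per arm and 58 in total reproduce.

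**2. Unadjusted precision.** SE = 5·√(2/23) = 1.474. With t(0.975; 44 df) = 2.015, the 95% half-width is 2.015 × 1.474 = 2.97 points. If the SD is 7.5, power is 0.60.

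**3. Adjusted for baseline.** Residual SD = SD·√(1 − ρ²) on 43 df. The SE is multiplied by √(43/42) = 1.012, an approximate allowance for estimating the slope. For ρ = 0.5: 1.474 × 0.866 × 1.012 = 1.292, and the half-width is 2.017 × 1.292 = 2.61.

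| ρ | 1 − ρ² | Residual SD (SD 5) | 95% half-width | Power, SD 5 | Power, SD 7.5 |
|---|---|---|---|---|---|
| unadjusted | – | 5.00 | 2.97 | 0.912 | 0.60 |
| 0 | 1.00 | 5.00 | 3.01 | 0.906 | 0.59 |
| 0.3 | 0.91 | 4.77 | 2.87 | 0.93 | 0.63 |
| 0.5 | 0.75 | 4.33 | 2.61 | 0.97 | 0.71 |
| 0.7 | 0.51 | 3.57 | 2.15 | 0.996 | 0.86 |

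**4. Chance baseline imbalance.** With baseline SD 5, the baseline difference between arms also has SE 1.474. The probability that it exceeds 2 points in either direction is 2·[1 − Φ(2 / 1.474)], about 17%.

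Only the fraction given by the regression slope passes through to 1 year. With equal SDs the slope is ρ, so a 2-point gap moves the unadjusted difference by 2ρ:
- ρ = 0.3: 0.6 points (12% of the margin)
- ρ = 0.5: 1.0 point (20%)
- ρ = 0.7: 1.4 points (28%)

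**5. Effect on the decision.** Given a 2-point gap against the hypofractionated arm, power of the t-test is approximately Φ[(5 − 2ρ − 2.97) / (1.474·√(1 − ρ²))]. For ρ = 0.5 this is Φ(1.03 / 1.277) = 0.79; for 0.3 and 0.7 it is 0.85 and 0.72. The adjusted analysis removes the shift, and its power stays close to the table values.

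**The case against.** **The test is valid and correctly sized.** In a 1:1 randomized trial the t-test is unbiased over randomizations and does not inflate type I error. It is the test used for sizing, and the sizing reproduces. This stands in full. A reader might infer that the primary result will be biased or that 58 patients are too few; the document supports neither. Its standard error already includes chance baseline variation.

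**Imbalance does not carry over in full.** With baseline SD 5, the 95% range of the baseline gap is ±1.96 × 1.474 = ±2.9 points, and one might read that as more than half the margin entering the result. Only the slope fraction does: about 0.9 to 2.0 points for ρ of 0.3 to 0.7.

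**The gain depends on an unstated correlation.** This also stands. At ρ = 0.3 the half-width falls by only 0.10 points. The large gains need ρ near 0.7, which nothing in the article establishes. The case for adjusting is that the loss at ρ = 0 is trivial.

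**Other safeguards exist.** The mixed models could use baseline, but they are supplementary and name no baseline covariate. The interim look at the SDs lets the monitoring committee recommend more patients; it does not recover precision from data already held. Excluding inflammatory bowel disease and prior pelvic irradiation removes some sources of poor baseline function, but does not balance the rest.

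**Change scores may be intended.** The article does not say outright which variable enters the test, although the endpoint wording points to the 1-year score. With equal SDs a change score has SD 5·√(2(1 − ρ)), which is 5.92, 5.00 and 3.87 at ρ = 0.3, 0.5 and 0.7. It beats the raw score only when ρ exceeds 0.5, and at each of these values its SD is above the ANCOVA residual SD. An unseen analysis plan might adjust, but it would then depart from the test the article names.

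**Conclusion.** The point holds as a worthwhile, inexpensive improvement to a valid analysis. The article fixes an unadjusted test for the primary comparison and the superiority step although a pre-treatment score is scheduled for every patient.

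At the planning SD the trial meets its power target without adjustment, so the value lies in narrower intervals and in results that depend less on the luck of the draw. It matters more if the SD proves larger than planned: at 7.5, adjustment recovers part of the lost power, from 0.60 to about 0.63–0.86.

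These sizes rest on an assumed correlation of 0.3 to 0.7, an assumed baseline SD of 5 and 23 evaluable patients per arm. They also take baseline scores to be essentially complete, which the schedule intends but cannot guarantee.

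**What to change.** Amend the Analysis plan so that:

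- The primary analysis is an ANCOVA of the 1-year EPIC bowel function score on arm and baseline EPIC bowel function. The 1-year arm contrast from the planned mixed model, with baseline as covariate, is an acceptable alternative; name one of the two.
- Non-inferiority is judged by comparing the two-sided 95% CI of the adjusted difference with the 5-point margin.
- The superiority step uses the same adjusted model.
- The unadjusted t-test or Wilcoxon test is kept as a sensitivity analysis.

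**Cost.** No new data are needed and N stays at 58. Because the primary test changes, this is a protocol amendment to be passed on to co-investigators, research boards and registries as the Protocol amendments section requires. It should be in force before any unblinded outcome data are seen.

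### The Wilcoxon fallback for the primary endpoint matches the 5-point mean margin only under an equal shift in all patients; if a subset is badly affected it can declare non-inferiority too easily

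*Protocol article*

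**What the plan says.** The Primary endpoint section names "Late bowel toxicity and quality of life measured using the Expanded Prostate Cancer Index Composite (EPIC) bowel function subdomain at 1 year post-treatment".

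The Sample size section sets the non-inferiority limit at "the minimum clinical significance (5 points) for the bowel function subdomain based on EPIC". It describes the method as follows: "Sample size calculation was performed by using a two-sided two-sample t-test for non-inferiority". The inputs are given in one sentence: "With an alpha = 0.05 and a standard deviation = 5, 23 patients in each arm are needed for a power = 0.90". A t-test with an SD is a comparison of means, so the margin is a margin on the mean difference.

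The Analysis plan section applies the t-test for non-inferiority to the acute and late quality-of-life endpoints, which include the primary one. It states the expectation "Quality of life data is anticipated to be normally distributed", followed by the fallback "In the event such data is not normally distributed, the Wilcoxon rank sum test for non-inferiority will be substituted as appropriate". It does not restate the 5 points for the rank test. It also does not say that the mean difference still decides non-inferiority after the switch.

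**The concern.** A t-test against a margin asks whether the mean deficit in Arm 2 is smaller than 5 points. A Wilcoxon non-inferiority test, in its usual form, adds 5 points to each Arm 2 score and asks whether the shifted scores tend to outrank the control scores. The two questions are sure to coincide only when the score distributions have the same shape and differ by a shift.

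If some patients are badly affected and the rest are not, the mean deficit can reach 5 points while most shifted Arm 2 scores still outrank controls. A severe decline then counts as a low rank, however deep it is. The fallback could therefore support non-inferiority when the mean deficit is at or beyond the margin on which the trial was sized.

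This matters because the Background section presents the trial as justification for larger randomized trials. It also reports that one of two earlier single-arm studies of ultra-hypofractionated pelvic treatment closed early because of late toxicity.

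**Working it through.** **1. The plan's own figure.** Inputs from the Sample size section: margin 5, SD 5, alpha 0.05 two-sided (0.025 in the tail that matters), power 0.90, true difference 0.

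Normal approximation: n = 2 × (1.960 + 1.282)² × 5² / 5² = 21.0, so 22 per arm. The exact noncentral-t power is 0.8997 at 22 and 0.9125 at 23, so 23 per arm. With 20% loss, 23 / 0.8 = 28.75, so 29 per arm and 58 in total. The plan's figure is reproduced, and it is a figure for means at one-sided 0.025.

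**2. Why the rank test can part from the mean.** Assume control scores are normal with SD s, and that a fraction q of Arm 2 loses d points while the rest are unchanged.

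- Mean deficit = q × d.
- Arm 2 SD = √(s² + q(1 − q)d²).
- Probability that a shifted Arm 2 score exceeds a control score = (1 − q)Φ(5/(s√2)) + qΦ((5 − d)/(s√2)). Wilcoxon leans towards non-inferiority when this exceeds 0.5.

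Results:

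- Everyone loses 5 (q = 1, d = 5): Φ(0) = 0.50. The tests agree.
- s = 5, 20% lose 25: mean deficit 5.0, SD √(25 + 0.16 × 625) = 11.2, probability 0.8 × 0.760 + 0.2 × 0.002 = 0.61.
- s = 5, 20% lose 30: mean deficit 6.0, probability 0.8 × 0.760 + 0.2 × 0.0002 = 0.61. The deeper loss leaves the rank comparison almost unchanged.
- s = 4, 70% lose 7.1: mean deficit 5.0, probability 0.3 × 0.812 + 0.7 × 0.355 = 0.49. Here there is no inflation.

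**3. Simulated rate of declaring non-inferiority.** 23 per arm, one-sided 0.025, Arm 2 scores raised by 5 and compared with control; 2,000 to 10,000 trials per case. All shapes are assumptions. The ceiling shape takes scores 100, 96.4, 92.9, 89.3 and 85.7 with probabilities 0.45, 0.25, 0.15, 0.09 and 0.06 (mean 96.2, SD 4.4).

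| Assumed shape | True mean deficit | Arm 2 SD | Wilcoxon | Welch |
|---|---|---|---|---|
| Normal, all lose 5 | 5.0 | 5.0 | 2.7% | 2.7% |
| Ceiling, all lose 5 | 5.0 | 4.4 | 3.0% | 3.05% |
| Normal s = 4, 50% lose 10 | 5.0 | 6.4 | 3.0% | about 3% |
| Normal s = 2, 50% lose 10 | 5.0 | 5.4 | 4.4% | about 3% |
| Normal s = 2.5, 40% lose 12.5 | 5.0 | 6.6 | 12.5% | 3.0% |
| Normal s = 2, 40% lose 12.5 | 5.0 | 6.4 | 18% | about 3% |
| Normal s = 5, 33% lose 15.15 | 5.0 | 8.7 | 6.2% | 2.9% |
| Normal s = 5, 25% lose 20 | 5.0 | 10.0 | 14.6% | 3.9% |
| Normal s = 5, 20% lose 25 | 5.0 | 11.2 | 23.9% | 4.4% |
| Ceiling, 30% lose 17 | 5.1 | 8.9 | 18% | 3.5% |
| Ceiling, 20% lose 25 | 5.0 | 10.9 | 45% | 5% |
| Ceiling, 15% lose 33 | 4.95 | 12.6 | 64% | 6% |
| Ceiling, 10% lose 50 | 5.0 | 15.6 | 81% | 10% |

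Repeat runs of the last four rows differed by a point or two, with 82% as the highest Wilcoxon value.

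Beyond the margin: with normal s = 5 and 30% losing 20 (deficit 6.0), Wilcoxon gives 6.9% and Welch 1.5%. With 20% losing 30 (deficit 6.0), Wilcoxon gives 24.7% and Welch 2.9%. With the ceiling shape and 20% losing 40 (deficit 8), Wilcoxon gives about 45% and Welch about 1%.

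**4. The switch itself.** A two-stage rule was also run: Wilcoxon if Shapiro-Wilk gives p < 0.05 in either arm, otherwise the t-test. It gave 24.1% for 20% losing 25 and 13.0% for 25% losing 20 (both normal s = 5), close to Wilcoxon alone.

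**The case against.** The strongest reply is that the large figures leave the plan's own assumption behind. They need Arm 2 SDs of about 9 to 16 against the planned 5. Near the planned SD the excess runs from none to moderate, and one case (70% lose 7.1, s = 4) gives 1.7%, below nominal. This stands, and it is why the size is given as a range. The Interim analysis section would show an inflated SD, but its remedy is more accrual, which does not change what the rank test tests.

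Skewness or a ceiling alone does no harm: the ceiling shape shifted by 5 points holds its level. This also stands. The arms must differ in shape.

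A reader might infer that the fallback is almost certain to be used, because bounded scores are never normal, or that bowel toxicity typically strikes a minority hard. The documents give neither the share of patients at the ceiling nor the pattern of harm. With continuous assumed scores, normality was rejected in anything from 10% to 99% of samples. The normality criterion may sit in an analysis plan that is not shown, so its absence is no part of this point.

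A reader might also infer that the trial would be blind to a severely affected subset. It would not be. The protocol compares CTCAE bowel toxicity between arms, collects EPIC bowel bother, fits linear mixed models to each quality-of-life domain and has a monitoring committee that meets every six months. None of these decides the primary claim.

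**Conclusion.** The point holds as a conditional one. The margin and sample size concern means. The stated fallback for the same endpoint concerns ranks, and the choice between them depends on the outcome data. That mismatch stands in the text and rests on no assumed score shape.

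Whether it leads to error depends on how Arm 2 differs from control. Under an equal shift there is no excess. With unequal effects and a mean deficit of about 5 points, the assumed shapes give about 3% to 18% near the planned SD and about 14% to 82% when 10% to 30% of patients lose 17 to 50 points, against a nominal 2.5%. Intermediate shapes fall between or below these bands, such as the 6.2% row in the table. All figures assume 23 evaluable patients per arm and that the rank test applies the 5 points as a shift of Arm 2 scores, which the article does not spell out.

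The sample size calculation is sound and is not in question.

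**What to change.** In the Analysis plan section, remove the Wilcoxon substitution for the primary endpoint. State that non-inferiority is decided by the two-sided 95% confidence interval for the difference in mean 1-year EPIC bowel function against the 5-point margin, whatever the distribution. Use an unequal-variance (Welch) interval, optionally adjusted for the baseline EPIC score already collected. Report the Wilcoxon result as supportive only.

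The cost is wording. The sample size stays at 23 evaluable per arm and 58 in total.

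The mean-based test is itself mildly anti-conservative under strong skew at this size, up to about 10% in the most extreme assumed case. A percentile bootstrap should not be offered as the cure: in the four ceiling cases (10%, 15%, 20% and 30% affected) it gave 9.7%, 6.4%, 5.2% and 3.7%, much the same as Welch. The change therefore reduces the error substantially in the unfavourable cases without removing it.
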